### Power analysis and sample size justification

A (one-sided) power analysis indicated 51 subjects per group will yield an 80% chance of detecting a decrease in depression scores of at least four points in treatment compared to control using a standard deviation of eight based on simulation. Clinically, a four point reduction in depression scores, as defined by the DASS, would represent a meaningful reduction in depressive states. A four point decrease may indicate that an individual has gone from expressing moderate to mild states of depression or mild to normal expression of depressive states [32].

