**Methods/Design:**

A placebo-controlled, single-blinded, randomised clinical pilot-trial has been designed to assess the influence of Neuro-Emotional Technique on a population with primary overt hypothyroidism. A sample of 102 adults (≥18 years) who meet the inclusion criteria will be randomised to either a treatment group or a placebo group. Each group will receive ten treatments (NET or placebo) over a six week period, and will be monitored for six months. The primary outcome will involve the measurement of depression using the Depression, Anxiety and Stress Scale (DASS). The secondary outcome measures to be used are; serum thyroid stimulating hormone, serum free-thyroxine, serum free-triiodothyronine, serum thyroid peroxidase auto-antibodies, serum thyroglobulin auto-antibodies as well as the measurement of functional health and well-being using the Short-Form-36 Version 2. The emotional states of anxiety and stress will be measured using the DASS. Self-measurement of basal heart rate and basal temperature will also be included among the secondary outcome measures. The primary and secondary measures will be obtained at commencement, six weeks and six months. Measures of basal heart rate and basal temperature will be obtained daily for the six month trial period, with recording to commence one week prior to the intervention.

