### Statistical Analysis

Two-sample t-tests will be used to compare change from baseline for NET treatment versus control at each of six weeks and six months for the primary outcome measure. Linear mixed-effects models will be used examine change over time in the treatment and placebo groups for the basal temperature and basal heart rate groups as well as the other secondary outcome measures. A significance level of 5% will be used throughout the analysis. Because the analyses will be seen as hypothesis generating, no adjustment for multiple testing will be used. The R software program [39] will be used to conduct the analyses. Complete case analysis will be employed for participants who strictly followed the trial protocol. Sensitivity analysis will be used for withdrawals, missing data and participants who violate the study protocol eg. changes in medication during the study period. This will be done using imputation techniques including last value carried forward, and multiple imputation.

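### The stated 80% power needs a one-sided 5% t-test with all 51 per group evaluable, but the plan allows for no losses, analyses only protocol-adherent completers and names no direction for the test

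*Protocol article*

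**What the plan says.** The section on power analysis and sample size justification gives the claim: "A (one-sided) power analysis indicated 51 subjects per group will yield an 80% chance of detecting a decrease in depression scores". The effect is "a decrease in depression scores of at least four points in treatment compared to control", and the spread is given as "using a standard deviation of eight based on simulation". It does not say whether that SD belongs to a single depression score or to the change in score.

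The abstract sets the number randomised: "A sample of 102 adults (≥18 years) who meet the inclusion criteria will be randomised to either a treatment group or a placebo group". The Sample section calls 102 a minimum. Neither place mentions an attrition rate or an evaluable target.

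The Statistical Analysis section describes the primary test: "Two-sample t-tests will be used to compare change from baseline for NET treatment versus control at each of six weeks and six months". On the level it says: "A significance level of 5% will be used throughout the analysis". It names no direction. On the analysis set it says: "Complete case analysis will be employed for participants who strictly followed the trial protocol". Withdrawals, missing data and protocol violators, with medication changes as the example, come in only through sensitivity analyses using last value carried forward and multiple imputation.

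**The concern.** The power figure and the analysis do not describe the same test on the same people.

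- **Analysis set.** 51 per group is the number that must reach the analysis, and the planned number randomised is the same. The main analysis then removes everyone who withdrew, has missing data or departed from the protocol. The course is ten sessions over six weeks with follow-up to six months, and the plan itself expects such cases because it provides for recording and imputing them.
- **Direction.** The calculation is openly one-sided. The analysis section does not carry this over, and its 5% level also covers the secondary mixed models. For the autoimmune markers the article says the direction of any response is unclear.
- **SD.** The test is on change from baseline, so the power depends on the SD of change.

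At stake is how a null result would be read. Readers would take it to come from a comparison with 80% power for the 4 points that the article calls clinically meaningful, when the design as analysed gives less under almost any loss.

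**Working it through.** **Inputs from the article:** difference Δ = 4, SD σ = 8, n = 51 per group, power 80%, one-sided (sample size section); level 5% (Statistical Analysis). The sample size section gives no level of its own; 5% is inferred because it reproduces 51.

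**Formula:** for a two-sample t-test with n per group, df = 2n − 2 and noncentrality λ = (Δ/σ)·√(n/2). One-sided power is P(T > t₀.₉₅) and two-sided power is P(|T| > t₀.₉₇₅), with T noncentral t(df, λ).

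**Step 1: reproduce the plan's figure.** Δ/σ = 4/8 = 0.5. At n = 51, λ = 0.5 × √25.5 = 2.525, df = 100, one-sided critical value 1.660. Power is 80.6%. Solving for 80% gives n = 50.15, rounded up to 51. So 51 is correct for a one-sided 5% t-test and includes no dropout inflation.

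**Step 2: how much spare is there?** One-sided power is 79.9% at 50 per group and 79.2% at 49. The margin is about one person per group.

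**Step 3: the same n, two-sided.** The critical value becomes 1.984 and power at 51 per group is 70.6%. Two-sided, 80% needs n = 63.8, that is 64 per group. With 51 per group, 80% is reached only for a difference of about 4.5 points (4.48).

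**Step 4: add losses.** The article states no loss rate. The exclusion rates below are assumptions; evaluable n is 51 × (1 − rate), rounded.

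| Assumed exclusion | Evaluable per group | One-sided power | Two-sided power |
|---|---|---|---|
| 0% | 51 | 80.6% | 70.6% |
| 5% | 48 | 78% | 68% |
| 10% | 46 | 77% | 66% |
| 20% | 41 | 73% | 61% |
| 25% | 38 | 70% | 58% |

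**Step 5: the meaning of SD 8.** If 8 is the SD of change, the table stands. If it is the SD of a single score, with equal SDs at both visits and baseline to follow-up correlation ρ, the SD of change is 8·√(2(1 − ρ)). The correlations are assumptions.

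| ρ | SD of change | One-sided power, n = 51 | Two-sided power, n = 51 |
|---|---|---|---|
| 0.3 | 9.5 | 68% | 56% |
| 0.5 | 8.0 | 80.6% | 70.6% |
| 0.7 | 6.2 | 94% | 90% |

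The ambiguity runs both ways. It is a reason to define the quantity and does not show that power is low.

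**The case against.** **Sidedness is not contradicted.** The sample size section says one-sided and the analysis section says neither. A one-sided 5% t-test is consistent with both, and sidedness is a detail that an article may leave to a fuller document. This stands in part. A reader might infer that the article promises a two-sided test and so contradicts itself, but it does not say so. The 70.6% is conditional on the usual reading of an undirected 5% test. The loss argument does not depend on it.

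**There is room above 102.** The Sample section gives 102 as a minimum, and the allocation sequence runs to 200. Both permit more recruitment, but neither is presented as an allowance for loss.

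**Excluded participants are not ignored.** Imputation brings them back in sensitivity analyses, and the six-week test need not depend on six-month data. Both points are true, but the main analysis at either time point still uses adherent complete cases only.

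**It is a pilot with hypothesis-generating analyses.** The article uses that label to justify making no multiplicity adjustment. It still makes a formal 80% claim, which should match the planned test.

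**SD of change is the natural reading,** since the sample size section speaks of a decrease relative to control and the test is on change. That is reasonable, and a few words would settle it.

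**Conclusion.** The 80% figure is wrong as written for the analysis described, although 51 is computed correctly for what it assumes. It holds only if the test is one-sided at 5% and at most about one person per group is lost. This part rests on Δ = 4, SD 8 for change, and the complete-case rule. At assumed exclusions of 5 to 25%, one-sided power is 78 to 70%. If the test is two-sided, power is 70.6% with no loss and 68 to 58% over the same range.

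Two stronger conclusions are not supported. A reader might infer that the true power is 60 to 70%. That combines a two-sided reading that the article never states with loss rates that it never gives. A reader might also suppose that a baseline-adjusted analysis of all randomised participants would recover most of the shortfall. The article plans no such analysis of the primary outcome, and any gain would depend on a correlation that it does not report.

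**What to change.** 1. In Statistical Analysis, state whether the primary t-test is one-sided or two-sided, so that it agrees with the sample size section.
2. In the sample size section, restate the power for that test at the number expected to be evaluable under the complete-case rule, and give the assumed exclusion rate. If two-sided with 51 evaluable per group, that is about 71% for 4 points, or 80% for about 4.5 points. If one-sided, it is below 80% once more than one per group is lost.
3. Say that 8 is the SD of change. If it is a single-score SD, give the assumed correlation and the resulting SD of change.

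The cost is a rewording of one paragraph and one sentence, and a less favourable stated figure. Restating the power needs no change to the design.

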### Statistical Analysis

Two-sample t-tests will be used to compare change from baseline for NET treatment versus control at each of six weeks and six months for the primary outcome measure. Linear mixed-effects models will be used examine change over time in the treatment and placebo groups for the basal temperature and basal heart rate groups as well as the other secondary outcome measures. A significance level of 5% will be used throughout the analysis. Because the analyses will be seen as hypothesis generating, no adjustment for multiple testing will be used. The R software program [39] will be used to conduct the analyses. Complete case analysis will be employed for participants who strictly followed the trial protocol. Sensitivity analysis will be used for withdrawals, missing data and participants who violate the study protocol eg. changes in medication during the study period. This will be done using imputation techniques including last value carried forward, and multiple imputation.

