### Randomisation and treatment allocation

Eligible participants will be randomly allocated to either the NET treatment group or the placebo (sham intervention) group. A random sequence generator will be used to produce a random sequence (1-200) with no repeats. These numbers will be recorded on individual pieces of paper and placed into envelopes which will then sealed and shuffled. After the participant has completed their initial blood test, the chief investigator will select an envelope for that participant. Participants allocated an even number will be assigned to the treatment group, and those receiving an odd number will be assigned to the placebo group.

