### Primary Outcome Measures

Significant proportions of individuals with 'managed' hypothyroidism continue to experience many of the symptoms associated with the overt, untreated version of the condition [1]. Depression is a common symptom associated with primary overt hypothyroidism [1]. Hypothyroid patients are more likely to experience constitutional and neuropsychiatric complaints as compared to euthyroid individuals [12]. For this reason, the primary outcome will involve the measurement of Depression using of the Depression Anxiety Stress Scale (DASS). The DASS is an instrument for measuring the negative states of depression, anxiety and stress. It is constructed of three self-report scales that enable researchers and clinicians to more concisely define, understand and measure these three clinical states. Each of the three scales contains 14 items that assess different aspects of depression, anxiety and stress [32].

The questionnaire is used to determine negative emotional states versus negative emotional traits. The DASS is based on a dimensional concept of psychological disorder. For this reason, the DASS is not used to allocate patients to specific diagnostic categories. This concept is different to other classificatory systems such as the Diagnostic and Statistical Manual of Mental Disorders (DSM) and International Classification of Diseases (ICD).

All items are rated on a four-point Likert scale from 0 - 3. Scores are determined according to how often particular symptoms were experienced in the past week, with high scores indicating a higher frequency of symptoms. Depression represents a sum of scores from 14 items within the DASS pertaining to depression [32]. States of dysphoria, hopelessness, devaluation of life, self-deprecation, anhedonia, inertia and a lack of interest and involvement are assessed by the 'depression' specific questions within the DASS. Normative data for the Depression scale of the DASS describes a mean of 6.34 with a standard deviation of 6.97. Clinically, depression scores between 0-9 are considered normal. Scores of 10-13 and 14-20 indicate mild and moderate states of depression respectively. Severe and extreme states of depression are defined by scores between 21-27 and 28+ respectively [32].

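### The primary t-test on change from baseline is valid but inefficient: baseline DASS depression is measured on everyone and is not used as a covariate

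*Protocol article*

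**What the plan says.** The Statistical Analysis section fixes the primary test: "Two-sample t-tests will be used to compare change from baseline for NET treatment versus control at each of six weeks and six months". It names no covariate for this test and keeps linear mixed-effects models for the secondary outcomes. On the error rate it says: "A significance level of 5% will be used throughout the analysis". It does not say whether the tests are one-sided or two-sided.

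The Measures and Primary Outcome Measures sections schedule the DASS for every participant at commencement, six weeks and six months.

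The power section gives the sample size and power: "A (one-sided) power analysis indicated 51 subjects per group will yield an 80% chance". The target effect is a 4-point difference between the arms, and the spread is described as "using a standard deviation of eight based on simulation". The section does not say whether 8 is the standard deviation of the change or of a single score, and it gives no baseline to follow-up correlation.

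Allocation is an envelope draw without stratification: "Participants allocated an even number will be assigned to the treatment group". Odd numbers go to placebo.

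**The concern.** Subtracting the baseline uses it with a fixed coefficient of 1. Unless baseline and follow-up are almost perfectly correlated, that over-corrects. The change score then remains negatively correlated with baseline, which adds avoidable noise to the treatment comparison. It also means that a chance difference between the arms at baseline carries through in part to the estimated effect in the trial actually run. An analysis that estimates the coefficient avoids both, using data the trial already collects.

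What is at stake is the width of the interval for the primary outcome. The power section shows no allowance for dropout, so spare precision would be useful.

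**Working it through.** **Inputs from the protocol article.** Difference 4 points, SD 8, 51 per group, 80% power, one-sided, 5% level. **Assumed, because not given:** the correlation r, taken from 0.3 to 0.9; equal variances at baseline and follow-up; and what the SD of 8 refers to, with both readings shown.

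**1. The plan's own figure.** n per group = 2(1.645 + 0.842)² × (8/4)² = 49.5, so 50 by the normal formula. The t distribution needs 50.15, so 51. One-sided power of the t-test at 51 per group is 80.6%. The stated sample size reproduces. The two-sided version needs 63 (normal) or 64 (t) and does not give 51.

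**2. Variance ratio.** With score variance s², the change has variance 2s²(1−r). After adjustment for baseline the residual variance is s²(1−r²). The ratio is (1−r²)/[2(1−r)] = (1+r)/2, which is below 1 for every r below 1.

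**3. Power at 51 per group if SD 8 is the SD of change.** Adjusted SD = 8 × √[(1+r)/2].

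| Analysis | Variance factor | SD | Power, one-sided | Power, two-sided | n per group, one-sided (normal formula) |
|---|---|---|---|---|---|
| t-test on change | 1 | 8.00 | 80.6% | 70.6% | 50 |
| Adjusted, r = 0.3 | 0.65 | 6.45 | 92.9% | 87.3% | 33 |
| Adjusted, r = 0.5 | 0.75 | 6.93 | 89.4% | 82.3% | 38 |
| Adjusted, r = 0.7 | 0.85 | 7.38 | 85.9% | 77.4% | 43 |
| Adjusted, r = 0.9 | 0.95 | 7.80 | 82.3% | 72.8% | 47 |

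The covariate costs one degree of freedom out of 100. That is ignored here and is negligible.

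**4. Power at 51 per group if SD 8 is the SD of a single score.** Change SD = 8√[2(1−r)]; adjusted SD = 8√(1−r²).

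| r | Change SD | Adjusted SD | One-sided power, change → adjusted | Two-sided power, change → adjusted |
|---|---|---|---|---|
| 0.3 | 9.47 | 7.63 | 68.2% → 83.7% | 56.1% → 74.6% |
| 0.5 | 8.00 | 6.93 | 80.6% → 89.4% | 70.6% → 82.3% |
| 0.7 | 6.20 | 5.71 | 94.4% → 96.9% | 89.8% → 93.8% |

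**5. Chance baseline difference.** Given an observed baseline difference D, the change-score estimate is shifted by −(1−r)D. Suppose D equals one standard error, s√(2/51), with s = 8/√[2(1−r)]. At r = 0.5, s = 8, D = 8 × 0.198 = 1.58, and the shift is 0.5 × 1.58 = 0.8 points. The same steps give 0.9 points at r = 0.3 and 0.6 at r = 0.7. Against the 4-point target this is roughly 15% to 23%. Adjustment removes this shift.

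**The case against.** The strongest reply is that nothing here is an error. A t-test on change is unbiased under randomisation and holds its type I error, and chance baseline imbalance is already counted within that 5%. On the reading that 8 is the SD of change, the test matches the sample-size calculation and reaches the 80% target. The article calls the trial a pilot and its analyses hypothesis generating. The gain depends on r and on the meaning of the SD, and at r = 0.9 it is under 2 points of one-sided power. All of this stands. It limits the point to efficiency, but it gives no reason to leave out a covariate already in hand.

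Three stronger readings are tempting, and the article does not support them.

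- **That the trial has only about 71% power and adjustment lifts it to 82%.** This presumes a two-sided test, an SD of change of 8 and r = 0.5. The only sidedness stated is one-sided, and the other two inputs are not given.
- **That the t-test lets a baseline imbalance pass as a treatment effect.** Over repeated randomisation it does not. The shift in step 5 is conditional on the imbalance observed.
- **That the t-test dilutes the effect by averaging over participants with no room to improve.** The article reports that "Normative data for the Depression scale of the DASS describes a mean of 6.34 with a standard deviation of 6.97" and that "Clinically, depression scores between 0-9 are considered normal", and eligibility sets no minimum score. If the sample followed those norms, about 45% to 50% would score below 4, and a nominal 4-point fall stopped at zero would average about 2.8 points. But these are general norms, and the article describes depression as common in hypothyroidism. With an assumed mean of 15 (SD 9), about 6% score below 4 and the average is 3.9. The size of any floor effect is therefore unknown. It would come from the absence of an entry threshold, not from the test, and covariance analysis with a common treatment effect averages over the same people.

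**Conclusion.** The point holds as one of inefficiency. The planned primary test is valid but discards information that the trial collects on every participant. Adjustment lowers the variance by 35%, 25%, 15% or 5% at r = 0.3, 0.5, 0.7 or 0.9, assuming equal variances over time. On the SD-of-change reading this is worth about 2 to 12 points of one-sided power at 51 per group. If the tests turn out to be two-sided, the gain is about 2 to 17 points, from a starting level below 80%. The direction of the gain is certain for any r below 1. Its size cannot be fixed from the article, because neither r nor the meaning of the SD is stated.

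**What to change.** In the Statistical Analysis section, replace the t-tests on change with an analysis of covariance of DASS depression at six weeks and at six months, with baseline DASS depression as a covariate. Equivalently, extend the mixed model already planned for the secondary outcomes to the primary one, with baseline, arm, visit and arm-by-visit terms. Report the adjusted difference at each visit with its 95% interval.

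The change costs a reworded sentence and one degree of freedom. It needs no additional participants, visits or measurements. It should be recorded before the statisticians learn the group allocation.

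An arm-by-baseline term could be pre-stated to look at whether the effect depends on the starting score. With 102 participants it would be imprecise, so it is optional and supportive at most, and it is not part of the correction.

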### Settings

Eleven private practices located in Sydney, Australia. The private practices are situated in ten different suburbs around the Sydney region. The distribution of practice locations has been chosen in an attempt to generate a sample that will be reflective of the general population of Sydney.

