### Measures

The standard guidelines for the assessment of individuals with thyroid dysfunction will be used by the primary care providers to establish the diagnosis of hypothyroidism [1]. The primary and secondary outcome measures (DASS, SF-36v2 and Serum Measures) will be applied pre-intervention to obtain baseline data, then reapplied at six weeks (post-intervention) and six months (study conclusion). Measurement of basal heart rate and basal temperature will be applied for each day of the six month study period, and will commence one week prior to the research intervention.

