It is anticipated that the majority of participants will be receiving treatment in the form of L-Thyroxine supplementation. For this reason, serum measures of TSH, serum FT4, serum FT3 should fall within normal reference ranges (See Table 1) provided there are no major alterations to this existing treatment strategy. In adequately treated participants, the addition of the experimental intervention should not influence serum thyroid hormone levels. However, in individuals who are not being medicated, or in individuals who are being under-treated upon entry into the trial, a decrease in TSH measurements and an increase in FT4 and FT3 measurements may be expected during the course of the trial.

In individuals who are being over-treated, elevated FT4 and FT3 levels and decreased TSH measurements will be demonstrated at baseline. It is expected that there will be no change in the serum measures in this subgroup.

It is unclear how the autoimmune markers will respond to the addition of NET to any existing treatment regimens.

In addition to the serum measures, participants will fill out the SF-36v2 and the additional items (anxiety and stress) of the DASS.

The SF-36v2 health survey is a questionnaire used to assess outcomes in eight different domains: role limitations because of physical or emotional problems, physical and social functioning, bodily pain, perception of mental and general health, and vitality [34].

Improvements in functional health and well-being as measured by the SF-36v2 will be depicted by increased scores by the respondents at six weeks and at six months. Deterioration in functional health and well-being will be revealed by a decrease in SF-36v2 scores.

Two additional secondary outcome measures are to be completed and recorded by participants at home for each day of the six month trial period are listed below:

Basal Heart Rate (BHR)

Basal Temperature (BT)

After signing up to take part in the trial, participants will be given a home diary, digital thermometer and instructions on how to record their BHR and BT. Participants will be instructed to make an effort to perform these measurements at the same time each day, and ideally before getting out of bed in the morning. For BHR measurements, participants will be instructed to find their radial pulse and then record the number of beats that occur in one minute and record this figure in the diary provided.

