Due to the chronotropic effect of the thyroid hormones on heart rate, untreated or undertreated individuals will demonstrate lower heart rates at baseline. It is anticipated that if NET therapy has a positive influence, there may be a trend over time toward slight increases in heart rate.

Basal temperature recording will be performed using a digital thermometer placed under the axilla. The thermometer will be placed under the axilla for approximately two minutes and the resultant temperature reading recorded.

Due to the thermogenic action of thyroid hormones, it is hypothesised that unmedicated or under-treated participants will experience an increase over time in basal temperature that may approach normal ranges of basal temperature (35.5 - 37.0°C) with the addition of NET treatment [35]. Adequately treated individuals should display normal basal temperatures at baseline that remain unperturbed by any additional treatment.

The secondary measures of basal heart rate and temperature measurement to be employed in this research study are commonly used by thyroid specialists as a crude measure of thyroid performance that is adjunctive to the hormone assays [36-38].

The recording of BHR and BT will begin one week prior to the initial intervention and continue for each day of the clinical trial.

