### Status of the trial and expected achievements

Start date: September 2006; Finish date of recruitment: March 2010; Finish date of follow-up: September 2010; Dissemination of results: Jan 2011.

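### As described, the basal temperature and heart-rate models name only time and group; a calendar-season term would cheaply remove any annual-cycle noise from the six-month contrast

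*Protocol article*

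**What the plan says.** All places are in the protocol article.

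- **Measures:** "Measurement of basal heart rate and basal temperature will be applied for each day of the six month study period".
- **Secondary Outcome Measures:** "The recording of BHR and BT will begin one week prior to the initial intervention and continue for each day of the clinical trial". On method: "Basal temperature recording will be performed using a digital thermometer placed under the axilla". The only control on timing is the hour of day: "Participants will be instructed to make an effort to perform these measurements at the same time each day". The effect looked for in heart rate is small: "there may be a trend over time toward slight increases in heart rate".
- **Settings:** "Eleven private practices located in Sydney, Australia", so all participants share one seasonal calendar.
- **Status of the trial and expected achievements:** "Start date: September 2006; Finish date of recruitment: March 2010; Finish date of follow-up: September 2010".
- **Statistical Analysis:** "Linear mixed-effects models will be used examine change over time in the treatment and placebo groups for the basal temperature". The sentence continues to basal heart rate and the other secondary outcomes. It gives no list of covariates and does not mention season, calendar date or ambient temperature.

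**The concern.** Half a year is the interval at which an annual cycle contributes most to a within-person change. Someone whose baseline week falls in winter gives the last readings in summer, and the reverse holds for a summer entrant. The seasonal part of the change therefore differs in sign and size with the month of entry. An average time trend cannot represent it, and neither can an arm-by-time term. If season is not modelled, it goes into the between-person variation in change and widens the confidence interval for the arm contrast.

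Axillary temperature, measured at home around waking, is the more plausible of the two outcomes to follow the season. That is a judgement; the article does not say so. What is at stake is precision on two secondary outcomes for which the hoped-for shifts are small.

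**Working it through.** **The plan's own figure.** The article states no effect size, SD or power for basal temperature or heart rate. Its one sample-size figure, 51 per group, is for the depression score. It reproduces: with a 4-point difference, SD 8, one-sided 5% and 80% power, the t-test needs 51 per group (power 80.6%). It has no bearing on this point.

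**Calendar.** September 2006 to March 2010 is 43 calendar months counted inclusively. September to March each occur four times and April to August three times, so entry can fall in any month. That enrolment is roughly even across those months is an assumption.

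**Variance added by an annual cycle.** Let the cycle be A·cos(phase), with amplitude A (peak-to-trough 2A) and entry phase uniform over the year. A change over L weeks then gains variance A²·(1 − cos(2πL/52)).

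- Six weeks: A²·(1 − cos(2π·6/52)) = 0.25·A².
- Six months (L = 26): A²·(1 − cos π) = 2·A², the maximum possible.
- A straight line fitted to the half-year of readings, expressed as change over six months: −(24/π²)·A·cos(phase) = −2.43·A·cos(phase), with variance 2.43²/2·A² = 2.96·A².

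With 43 evenly filled months and a January peak, the six-month figure is 4 × 0.489·A² = 1.95·A², so the uniform approximation is adequate.

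**Size for basal temperature.** A and s (the non-seasonal SD of six-month change) are both assumed. The variance ratio is 1 + 2A²/s², and the loss of effective sample is 1 − 1/ratio.

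| A (°C) | s (°C) | Variance ratio | Effective sample lost |
|---|---|---|---|
| 0 | any | 1.00 | 0% |
| 0.05 | 0.3 | 1.06 | 5% |
| 0.05 | 0.2 | 1.13 | 11% |
| 0.10 | 0.3 | 1.22 | 18% |
| 0.10 | 0.2 | 1.50 | 33% |
| 0.15 | 0.3 | 1.50 | 33% |
| 0.15 | 0.2 | 2.13 | 53% |

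**Basal heart rate.** Assume an amplitude of 0.5 to 2 beats/min and an SD of change of 8 down to 4. The ratio runs from 1 + 2·0.5²/8² = 1.01 to 1 + 2·2²/4² = 1.50.

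**Simulation of the remedy.** The set-up was 51 per arm, weekly mean temperatures, entry uniform over 43 months, amplitude varying between people with a 30% coefficient of variation, and 2,000 runs per scenario. The arm difference in per-person slopes was estimated with and without annual sine and cosine terms, for slope SDs of 0.2 and 0.3.

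| A (°C) | Unadjusted ÷ adjusted variance |
|---|---|
| 0 | 0.98–0.99 |
| 0.05 | 1.04–1.12 |
| 0.10 | 1.27–1.53 |
| 0.15 | 1.59–2.17 |

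Across all scenarios run, the unadjusted estimate averaged about zero and its type I error was 4.4% to 5.8%. The cost of leaving season out is therefore precision and not validity. Adding the terms when there is no cycle costs 1% to 2% in variance.

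**The case against.** The strongest reply is that the article shows no error. Its one sentence on mixed models is a condensation that excludes nothing, and covariate lists for secondary outcomes are commonly left to a full analysis plan. No section mentions an annual cycle, both inputs to the size are assumed, and the top of the range pairs the largest amplitude with the smallest SD. The outcomes are secondary, the analyses are declared hypothesis generating, and allocation is randomised and concurrent.

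Much of this stands, and it rules out several stronger readings that a reader might infer:

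- *That the models use time on study and nothing else.* The text names only time and group, but it does not say that these are the only terms.
- *That season biases the treatment comparison.* Randomised concurrent controls prevent that, and the simulation agrees.
- *That a null result would be uninformative.* With no target effect, SD or amplitude in the documents this cannot be judged. At the low end of the assumed range the loss is minor.
- *That everyone's readings move by the full swing.* The absolute shift averages 0.64 of the peak-to-trough swing and is near zero for people who enter midway between peak and trough.
- *That the serum outcomes share the problem.* Nothing in the documents supports extending it to them.

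The timing argument survives. Six months is half a cycle, entry dates cover the year, and a common time effect cannot absorb a shift that depends on entry month. A season term is also something analysts would be unlikely to add by default, and it is better specified before results are seen.

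**Conclusion.** The point holds as an inexpensive improvement in precision, not as an error. If basal temperature has an annual cycle of 0.05 to 0.15 °C amplitude and the non-seasonal SD of six-month change is 0.2 to 0.3 °C, leaving season out multiplies the variance of that change by about 1.06 to 2.1, a loss of about 5% to 53% of the effective sample. With no cycle the loss is zero. At six weeks the added variance is about one eighth of that at six months (0.25·A² against 2·A²).

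The result rests on three assumptions: the amplitude, the SD, and entry dates spread fairly evenly over the year. Priority is low, and only basal temperature and basal heart rate are concerned.

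**What to change.** In Statistical Analysis, state that the mixed models for basal temperature and basal heart rate will include two further fixed effects, sin(2πd/365.25) and cos(2πd/365.25), where d is the calendar day of the reading. Make them common to both arms and keep the arm-by-time contrast as the reported effect. Because entry is spread over the year, these terms are separable from time on study. Leave the serum models and the primary depression analysis unchanged. If a fuller analysis plan already adjusts for season, saying so closes the point.

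The cost is one sentence and two degrees of freedom per model. No new data are needed, since daily diary entries can be placed on the calendar.
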